**Methods/Design:**

A randomized controlled clinical trial will be conducted. It will involve 60 women ≥ 35 years of age with a diagnosis of FM and TMD. After recruitment, patients will be randomly allocated to one of four groups: a control group (no intervention), a group that will receive a phototherapy intervention (PHO), a group that will be prescribed muscle-stretching, aerobic, and facial exercises (EXT), or a group that will receive phototherapy plus exercise interventions (PHO + EXT). The trial will last 10 weeks, and the following outcomes will be evaluated on two separate occasions (baseline and within 24 h after the last day of the protocol). Pain intensity will be analyzed using a visual analogue scale and the McGill Pain Questionnaire, and pain thresholds will be punctuated using a digital algometer. FM symptoms will be assessed using the Fibromyalgia Impact Questionnaire, and quality of life will be determined with the 36-item Short Form Health Survey. Serotonin levels will be evaluated in salivary samples using a competitive enzyme-linked immunosorbent assay.

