A comprehensive review of the literature revealed no studies evaluating the role of phototherapy with multiple light sources (LLLT and LED) on the same device in the pain condition in patients with FM and TMD. In addition, there are no prior data involving a combined intervention of phototherapy and exercise training in patients with FM and TMD. The hypothesis of the proposed study is that combined intervention is capable of improving chronic pain in patients with FM and TMD. Knowledge regarding the clinical effects of these interventions can contribute to improved rehabilitation and quality of life among such patients.

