### Objective

In this trial, we seek to assess the potential role of exercise training plus phototherapy to reduce chronic pain in women with FM and TMD.

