### Randomization, blinding, and experimental groups

The EXTRAPHOTO trialists will enroll patients immediately after diagnosis of the two comorbidities and referral from recruitment centers. Patient enrollment and randomization, as well as data management, will be carried out by the Program in Biophotonics Applied to Health Sciences of the Nove de Julho University. The blinding will be applied to patients receiving phototherapy and a researcher reported to guide the exercise training. Thus, a researcher will be responsible for programming the phototherapy device, which can be turned on (phototherapy) or off (placebo) prior to application based on the randomization. A second researcher will guide the exercise training and will be blinded for phototherapy and/or placebo procedures. A third investigator will be blinded to allocation and will independently assess the outcomes. The statistical analysis will be performed by a fourth researcher, who will also be blinded to allocation of the patients.

The eligible participants will be instructed not to change their lifestyle or pharmacologic therapy during the study and will be randomized to one of the following groups:Control (CON): patients not subjected to any intervention; the phototherapy device will be turned off (placebo) as a blinded procedure for these participantsPhototherapy (PHO): patients subjected to phototherapyExercise training (EXT): patients subjected to aerobic exercise; the phototherapy device will be turned off (placebo) as a blinded procedure for these participantsPhototherapy plus exercise training (PHO + EXT): patients subjected to phototherapy and aerobic exercise training

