### Statistical analysis

Pain will be the primary endpoint and will be determined using a VAS, an algometer, the FIQ, and the McPQ. Quality of life as assessed by SF-36, salivary serotonin level, and overall parameters of pain will be secondary endpoints. Statistical analysis will be performed using IBM SPSS software (version 13.0; IBM, Armonk, NY, USA), and a two-sided *P* value <0.05 will be considered significant. The intragroup and intergroup comparisons will be carried out with two-way repeated-measures analysis of variance with post hoc Bonferroni correction or the Kruskal-Wallis test with a post hoc Dunn test. The choice of tests will be based on the distribution (normal or non-normal) of the data by the Shapiro–Wilk test. For categorical data, χ^2^ statistics will be used.

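### The four arms form a 2x2 design and the hypothesis concerns the combination, but the analysis compares four unordered groups post hoc and designates no test of that hypothesis

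*Protocol article*

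**What the plan says.** The abstract states that "patients will be randomly allocated to one of four groups". In Randomization, blinding, and experimental groups, the control and exercise arms have the device switched off as a sham, the phototherapy arm has active light, and the fourth arm is described as "patients subjected to phototherapy and aerobic exercise training". That is active or sham light crossed with exercise or no exercise, with all four cells filled.

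The Background states one hypothesis, that the "combined intervention is capable of improving chronic pain in patients with FM and TMD". The Objective is to "assess the potential role of exercise training plus phototherapy to reduce chronic pain in women with FM and TMD". Neither names a comparator.

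Statistical analysis plans within-group and between-group comparisons by "two-way repeated-measures analysis of variance with post hoc Bonferroni correction", or Kruskal-Wallis with a Dunn post hoc test if the data are not normal. A two-sided P "value <0.05 will be considered significant". The section names no planned contrast, main effect of phototherapy or exercise, or interaction between them, and does not say how many comparisons the Bonferroni correction covers.

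**The concern.** The sham in the arms without active light makes the phototherapy effect estimable at both levels of exercise, and so makes the interaction estimable. The written analysis does not use this. With a baseline and an end-of-trial measurement, two-way naturally means group by time, with group as a single four-level factor; phototherapy by exercise by time would be a three-way analysis. The Kruskal-Wallis branch is one-way and gives no interaction estimate at all.

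Two things are at stake. First, a reader cannot tell in advance which result would confirm or refute the combination hypothesis, because the combination arm is only one of four groups in a set of post hoc comparisons. Second, the comparison that bears on the hypothesis pays for a correction shared with others that do not, while the component effects are never estimated from all randomized women.

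**Working it through.** **The plan's own figure.** Population and sample size uses a precision formula for a prevalence: n = (1.96 × √(0.8 × 0.2) / 0.1)² = 61.5, rounded up to 62. The stated 60 is close to this. The formula concerns how precisely TMD prevalence is estimated and says nothing about power between arms. The same section gives 60 women in total and 20 per group. With four groups, 60 / 4 = 15 per arm, while 4 × 20 = 80 in total, so both sizes are carried below.

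**Inputs.**
- From the article: four arms; two-sided alpha 0.05; 15 or 20 women per arm.
- Assumed, because the article gives no effect size, SD or power: standardized differences d of 0.5 to 1.2 on the analysed scale, and no dropout.
- Assumed family for the Bonferroni figure: all pairs of four arms, 4 × 3 / 2 = 6, so 0.05 / 6 = 0.0083.

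**Method.** Non-central t with error pooled over the four arms, df = N − 4 (56 or 76). For k women on each side of a contrast, the non-centrality parameter is d / √(2/k). A pair of arms has k = 15 (or 20); a main effect has k = 30 (or 40).

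**Difference detectable with 80% power (SD).**

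| Comparison | 15 per arm | 20 per arm |
|---|---|---|
| One pair at 0.05/6 | 1.31 | 1.13 |
| One planned pair at 0.05 | 1.04 | 0.90 |
| Main effect at 0.05, no interaction | 0.74 | 0.64 |

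With a family of only three comparisons at 15 per arm (0.05 / 3 = 0.0167), the pair needs 1.21 SD, still above 1.04.

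**Power at 15 per arm.**

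| d | Pair at 0.05/6 | Pair at 0.05 | Main effect at 0.05 |
|---|---|---|---|
| 0.5 | 10% | 27% | 48% |
| 0.8 | 30% | 58% | 86% |
| 1.0 | 51% | 77% | 97% |
| 1.2 | 71% | 90% | 99.5% |

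At 20 per arm and d = 0.8 the three figures are 43%, 70% and 94%.

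The first two columns concern the same contrast, so the drop from 77% to 51% at 1.0 SD is purely the cost of the six-fold correction. The third column is a different quantity, and the next two checks show when its advantage disappears.

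**Additive components, 0.5 SD each, 15 per arm.** The combination differs from control by 0.5 + 0.5 = 1.0 SD. Power is 51% at 0.05/6 and 77% at 0.05, against 48% for each main effect. The combination against a single component (0.5 SD) has 10% at 0.05/6 and 27% at 0.05.

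**Overlapping components, 15 per arm.** If each component alone gives 0.8 SD and the combination adds nothing further, the main effect is the average of 0.8 and 0, that is 0.4 SD, with 33% power. The interaction test itself has 33% power for an interaction of 0.8 SD.

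**The case against.** The Background hypothesis names no comparator, and Study design describes a comparison of exercise, phototherapy and both together. For a multi-arm comparison of that kind, an overall test followed by corrected pairwise tests is conventional and protects against false positives. The article is also condensed, and the exact family of comparisons could sit in an analysis plan that is not shown.

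Part of this stands. The control arm is the most direct comparator for the hypothesis, but the article does not say so. That all six pairs will be tested is also an inference, because the section speaks only of comparisons between groups with a post hoc correction.

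Three stronger readings should not be drawn:
- A reader might infer that nothing in the analysis asks whether the combination beats either component. If all pairs are tested, the combination against exercise and against phototherapy are among them. What is missing is a designated test and an interaction estimate.
- A reader might infer that the plan forfeits most of its power. That depends on an effect size the article does not give. Against a main effect at 15 per arm it holds for about 0.5 to 0.8 SD; at 1.0 SD the loss is about half (97% to 51%) and at 1.2 SD under a third (99.5% to 71%).
- A reader might take the main-effect figures as the power available for the hypothesis. They answer a different question and presuppose no interaction.

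The appeal to an unseen analysis plan does not remove the point. The article does fix a method, and neither of its branches, as written, estimates a component effect across arms or an interaction.

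**Conclusion.** The point holds as a mismatch between design, hypothesis and stated analysis, and should be corrected. That conclusion rests on the arm definitions, the Background hypothesis and the natural reading of two-way as group by time; it needs no effect size.

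The size is conditional. If the family is six pairs, the correction raises the detectable difference for the contrast of interest by about a quarter at either arm size (1.31 / 1.04 = 1.26 and 1.13 / 0.90 = 1.26). A smaller family costs less. The ordering of the three approaches is the same at 15 and 20 per arm for a given standardized difference, but the main-effect advantage shrinks or vanishes for the combination contrast under additivity, and when the components overlap.

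**What to change.** Before unblinded data are seen (Trial status says allocation is under way), reword Statistical analysis as follows.

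1. Name one primary contrast for the Background hypothesis and state its comparator; PHO + EXT against CON is the most direct reading. Test it at two-sided 0.05 for each pain measure, subject to whatever multiplicity rule covers the four primary pain instruments (VAS, algometer, FIQ, McGill).
2. From the same model, report PHO + EXT against EXT and against PHO, the phototherapy and exercise main effects, and the PHO x EXT interaction, each with a 95% CI, plus the four arm means.
3. Use that model in place of the Kruskal-Wallis branch as well, on ranks or transformed data if needed.
4. Label the remaining pairs exploratory.
5. Reconcile 60 in total with 20 per group, so that the power of the primary contrast can be stated.

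The analysis changes are wording only: no added visits or measurements. The price is that the other pairs lose confirmatory status. PHO + EXT against CON alone does not show that either component adds to the other, and the main effects must be read beside an interaction estimate that is imprecise at this size.

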### Population and sample size

In a literature review, we found that FM prevalence is higher in women between ages 35 and 60 years than in men [21]. All women patients aged ≥ 35 years and referred for FM and TMD diagnostic evaluation were eligible for inclusion in the present trial. Patient eligibility comprises an evaluation of medical history, physical examination, and dental and rheumatologic routine evaluations. Moreover, patients had to have undergone FM screening as reported by the American College of Rheumatology using the Fibromyalgia Impact Questionnaire (FIQ) 1. The TMD diagnosis had to be reported on the basis of TMD research diagnostic criteria (axes I and II) [22]. The sample size calculation was based on a previous study by Consalter et al. [23] in which the TMD prevalence was 80 % in patients with FM. A 95 % reliability and a 10 % error rate was assumed to estimate the sample size (n) as follows [24]:$$ n={\left(\frac{z_{a/2}\sqrt{p\left(1-p\right)}}{\varepsilon}\right)}^2={\left(\frac{1.96\ast \sqrt{0.8\ast 0.2}}{0.1}\right)}^2 $$

A total of 60 women will be randomized for this trial, with 20 women allocated per group.

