### Outcome parameters

The outcome parameters described below will be evaluated at baseline and 24 h after the last day of the experimental protocol.

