#### Overall parameters of pain

To assess overall parameters of pain, we will gather information on daily duration of pain, pain tender points, number of days with a high pain level, sleep quality, main features that show accentuation or worsening of pain, incidence of stiffness and pain, jaw locking, and morning fatigue.

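### Only χ² is named for categorical data, although secondary endpoints that are probably categorical are measured before and after treatment; baseline status goes unused between arms and, if χ² is used within arms, so does the pairing

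*Protocol article*

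**What the plan says.** All places are in the protocol article.

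- **Endpoint status.** Statistical analysis: "overall parameters of pain will be secondary endpoints".
- **Items.** Overall parameters of pain: a mixed list that includes durations and counts, and also "incidence of stiffness and pain, jaw locking, and morning fatigue". No measurement scale is given for any item.
- **Timing.** Outcome parameters: the outcomes "will be evaluated at baseline and 24 h after the last day of the experimental protocol", so each woman contributes two answers per item.
- **Method for categorical data.** Statistical analysis: "For categorical data, χ^2^ statistics will be used". No paired, stratified or baseline-adjusted form is named.
- **Method for other data.** The same section covers comparisons both within and between groups by "two-way repeated-measures analysis of variance with post hoc Bonferroni correction or the Kruskal-Wallis test with a post hoc Dunn test", chosen by a normality test.
- **Threshold.** A "two-sided *P* value <0.05 will be considered significant".
- **Size.** Population and sample size: "A total of 60 women will be randomized for this trial, with 20 women allocated per group". The design has four groups, so this means 15 per arm (60 ÷ 4) or 80 women in total (4 × 20). Both arm sizes are used below.

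**The concern.** For normally distributed scores, the plan uses a model that takes in both measurements and so reflects change within each woman. The sentence on categorical data has no counterpart to this, although the items it probably covers are measured at the same two visits.

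Between arms, an ordinary χ² on post-treatment status counts a woman without jaw locking at baseline as a good outcome, although she could not have improved. If baseline status predicts final status, ignoring it leaves avoidable noise in a comparison of 15 or 20 women per arm.

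Within an arm, an ordinary χ² treats two answers from the same woman as if they came from two different women. When the answers are positively correlated, the test overstates the variance of the change and rejects too rarely, so real before-after changes can be missed.

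At stake is efficiency on secondary endpoints, one of which (jaw locking) is specific to the temporomandibular disorder.

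**Working it through.** **The plan's own figure.** The only sample-size calculation is a precision formula for one prevalence: n = (1.96 × √(0.8 × 0.2) / 0.1)² = 61.47, or 62 rounded up, against the stated 60. It gives no power for any endpoint, so there is no power figure to reproduce. Event rates, the before-after association and dropout for the categorical items are not given. They are assumed and varied below.

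**Step 1: power of plain χ² between two arms.** Assume post-treatment rates of 0.60 and 0.30. With n per arm and average rate 0.45:

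power ≈ Φ{[0.30 − 1.96 √(2 × 0.45 × 0.55/n)] / √[(0.60 × 0.40 + 0.30 × 0.70)/n]}

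- n = 15: (0.30 − 1.96 × 0.1817)/0.1732 = −0.32, power 37%.
- n = 20: (0.30 − 1.96 × 0.1573)/0.1500 = −0.06, power 48%.

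**Step 2: what baseline status adds.** If baseline and final status correlate at phi, stratifying by baseline removes roughly a share phi² of the outcome variance. That is like having n/(1 − phi²) women per arm in the formula of step 1.

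| phi | n = 15 acts as | power | n = 20 acts as | power |
|---|---|---|---|---|
| 0 | 15.0 | 37% | 20.0 | 48% |
| 0.3 | 16.5 | 41% | 22.0 | 52% |
| 0.5 | 20.0 | 48% | 26.7 | 60% |
| 0.6 | 23.4 | 54% | 31.3 | 67% |

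**Step 3: simulation.** Settings: 2,000 runs each; 15 or 20 per arm; baseline prevalence 0.5 to 0.7; two arms (0.60 v 0.30, or 0.60 v 0.20) and four arms (0.60/0.45/0.45/0.20). The comparison is Pearson χ² on final status against a (generalised) Mantel-Haenszel test stratified by baseline.

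| phi | gain from stratifying (percentage points) |
|---|---|
| 0 | about −2 to +1 |
| 0.3 | about +2 to +4 |
| 0.5 | about +6 to +13 |
| 0.6 | about +9 to +20 |

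Some settings at phi 0.5 and 0.6 cannot occur with the assumed rates, and their probabilities were truncated. The settings that can occur gave +8 to +13 and +16 to +20. Example with 15 per arm, 0.60 v 0.30 and baseline prevalence 0.5: 37% rises to 46% at phi 0.5 and to 53% at phi 0.6, close to step 2.

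**Step 4: validity between arms.** With no treatment effect, simulated type I error of the unadjusted four-arm χ² was 4.8% to 5.3%. In a separate simulation (20,000 trials per scenario) the stratified test had 3.9% to 4.5%, so its gain is not bought with false positives. An ordinary baseline-adjusted logistic likelihood-ratio test had about 6% to 8% at these sizes.

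**Step 5: ordinary χ² within one arm.** With no true change and before-after correlation ρ, the variance of the change is (1 − ρ) times what the unpaired test assumes. The large-sample true error is therefore 2 × [1 − Φ(1.96/√(1 − ρ))]. The simulation used 200,000 samples, n = 15 and an assumed prevalence of 0.6.

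| ρ | 1.96/√(1 − ρ) | large-sample error | simulated error, n = 15 |
|---|---|---|---|
| 0.3 | 2.34 | 1.9% | 2.0% |
| 0.5 | 2.77 | 0.56% | 0.7% |
| 0.7 | 3.58 | 0.03% | 0.1% |

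The nominal level is 5%.

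**The case against.** **The scale is inferred.** The article does not say that these items are categorical, and it does not tie the χ² sentence to them. That sentence may be meant for descriptive data such as education level and marital status, for which an ordinary χ² is suitable. This stands as a limit. The wording of the items still suggests yes/no or categorical recording, and if they are recorded that way, χ² is the only method offered.

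**The wording is loose.** McNemar and Mantel-Haenszel statistics are also χ² statistics, and an article may leave the exact form to a fuller document. This also stands in part. The article does name a method, however. On the loose reading it still does not say which test answers which question: McNemar's test cannot compare four arms, and an ordinary χ² cannot handle paired answers.

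**The named test is valid between arms.** This stands fully. A reader might infer that ignoring baseline biases the comparison or that chance imbalance invalidates it. Randomisation and the simulated error of about 5% contradict that. Nor does the within-arm use create false positives; it loses true ones.

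**The power loss is not a fixed figure.** A reader might take 6 to 18 points, or a similar range, as the general cost. The documents contain no input that supports this. Such values need a moderate to strong baseline-to-outcome association, and the loss vanishes when there is none.

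**The endpoints are secondary.** True. Stiffness and fatigue also enter the Fibromyalgia Impact Questionnaire, and algometry at the temporomandibular joints is part of the primary endpoint. This lowers the weight of the point without removing it.

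**Conclusion.** The point holds as a correctable weakness in a stated method. It is not an error that invalidates the analysis. If the items are categorical and χ² means an ordinary contingency-table test, the between-arm comparison is valid but gives up power: nothing at phi 0, 2 to 4 points at 0.3, and roughly 6 to 20 points at 0.5 to 0.6. These figures rest on assumed rates with 15 or 20 women per arm. A moderate or stronger association is plausible in women with at least five years of diagnosis and stable drug treatment, but the documents do not show it.

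The within-arm problem is conditional on χ² being used there. In that case the test runs at about 2.0% to 0.1% instead of 5% for correlations of 0.3 to 0.7 with 15 women. Because the endpoints are secondary and the remedy is only wording, the change is worth making but the trial does not depend on it.

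**What to change.** State the scale of each overall parameter of pain, and replace the sentence on categorical data with wording such as:

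*Categorical outcomes measured at baseline and after treatment will be compared between groups with a (generalised) Cochran-Mantel-Haenszel test stratified by baseline status, in its exact form when cells are sparse. Change within a group will be tested with McNemar's test for binary items, and with Bowker's test or a marginal homogeneity test for items with more than two categories. The ordinary χ² test is reserved for categorical characteristics measured once.*

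Naming one between-group method avoids a later choice among analyses. The stratified test is preferable to ordinary baseline-adjusted logistic regression, whose error rate ran above 5% at these sizes.

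The cost is a few lines of analysis text, with no new data, visits or patients. The downside is small: strata with very few women contribute little, and the gain is near zero (simulated −2 to +1 points) if baseline barely predicts outcome.

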### Ethical approval

The ethics committee of the Nove de Julho University (Sao Paulo, Brazil) reviewed and approved this study protocol (protocol number 419.828/2013). The trial was conceived and will be conducted according to the principles set forth in the Declaration of Helsinki [32]. All patients will be requested to provide written informed consent prior to randomization, using standard forms. Patients may withdraw from the study at any time without penalty. Our standpoint is that any intervention has beneficial effect. It is an ethical issue in which the control group knows the positive results of the study. Therefore, the control group will be given the opportunity to receive intervention after the end of the trial. The trial is registered at ClinicalTrials.gov under the number NCT02279225 (27 October 2014).

